#### Effectiveness

##### Training Effectiveness (Coaches)

Effectiveness of the training for SSBC Australia coaches will be assessed via attainment of competency and their change from pre- to posttraining in self-rated knowledge and confidence scores (1-7). These scores incorporate knowledge and confidence in cultural safety, prevention and management of type 2 diabetes and prediabetes, MI, physical activity, and nutrition (all collected via 7-point Likert scales from 1=strongly disagree to 7=strongly agree).

##### Program Effectiveness (Clients)

###### Overview

Client-level effectiveness outcomes are listed below. The primary effectiveness outcome is self-reported moderate to vigorous physical activity time. Effectiveness outcomes are collected either via survey or by in-person measurement at preprogram, end-of-program (primary end point), and 12 months after the program ends. The self-report outcomes are also collected by surveys at 3 and 6 months after the program ends, except that health-related quality of life and loneliness are skipped at 3 months (Table 6).

###### Clinical Indicators (Objective Physical Assessments)

In-person measures of body composition (weight [kg] and waist circumference [cm]), cardiorespiratory fitness (resting blood pressure and 2-minute step test), and strength and balance (hand grip strength and balance test) will be conducted at baseline, end-of-program, and 12 months with the primary time point change before program to end-of-program.

Height (cm) will be measured at baseline only (Seca 217 Stadiometer) to enable calculation of body mass index. Weight will be measured by digital scales (ADE Digital Scales with a capacity of 250 kg) with outer clothing (ie, jackets) and shoes removed. Waist circumference will be measured by a tape measure at the abdomen at its narrowest point between the lower costal (10th rib) border and the top of the iliac crest, perpendicular to the long axis of the trunk.

The Queens College protocol will be used for the 2-minute step test [66]. The 2-minute step test has been shown to have high intraclass reliability (*R*=0.9) and criterion validity (*r*=0.74) [67]. Blood pressure will be measured by an automatic blood pressure monitor (model HEM-907; Omron) after the client has been seated for at least 5 minutes. The average of 2 readings will be used.

Hand grip strength will be measured with a dynamometer (Camry model EH101), with the average of 3 trials on each hand will be used. A systematic review reported this test to be a valid and reliable measure [68]. The 4-stage balance test with ceiling [69] will be used for assessment of balance, with participants asked to hold each position for at least 30 seconds if they can. This test has been shown to have acceptable reliability (test-retest *r*=0.66), validity, and discriminant ability [70].

###### Self-Report Measures

MVPA will be captured with the Physical Activity Vital Sign (PAVS) questionnaire [71]. The PAVS is recommended by the American College of Sports Medicine as part of their Exercise is Medicine resources and has demonstrated good concurrent validity [72]. An additional question will be added to the PAVS to identify how much of that time is spent specifically in vigorous (strenuous) activity.

Strength training will be captured through the question from the PAVS on strength training [71].

Movement behaviors across the 24-hour day will be measured using a bespoke single-item (4-part) question that has shown good validity against an activPAL criterion in in-house testing and good acceptability from participants. Here, participants will be asked their time (in hours and minutes) spent in the following activities for a typical day, with the total needing to add up to 24 hours: sleeping, moderate or strenuous (vigorous) activity (noting this is prefilled from their responses to the PAVS), other lighter moving or standing, and sitting or lying down (sedentary).

The percentage of prolonged sedentary time (sitting or lying for 30 minutes or more continuously) will be captured using a single-item question shown to have adequate measurement properties in terms of both test-retest and criterion validity [73].

Sleep quality will be measured by the single-item 11-point sleep quality scale (0=terrible and 10=excellent), which has demonstrated good criterion validity (*r*=–0.76 to –0.92) and test-retest reliability (intraclass correlation=0.62) [74].

Dietary behaviors will be measured by scores from the 9-item Mini-Eating Assessment Tool, which has shown good correlation with the Healthy Eating Index assessed by a validated food frequency questionnaire (*r*=0.71) [75]. Data are collected on the frequency of consumption of fruits, vegetables, legumes, nuts and seeds, fish or seafood, whole grains, refined grains, low-fat dairy, high-fat dairy and saturated fats, and sweets and sweet foods. Permission for use was granted by the Mini-Eating Assessment Tool team (March 11, 2025). An additional item on sugar-sweetened beverages was also included in the items to enable comparison to population health surveys [76].

Participants will be asked how often they do the behaviors targeted in the program, with each of the 6 questions using a 5-point Likert scale (1=never or very rarely to 5=very often or always). The questions, developed for this study, ask about tracking and setting goals for physical activity, reading food labels, adding sugar (item reversed scored), choosing low glycemic index options, and choosing a well-balanced plate.

Psychosocial measures include those related to social support, self-efficacy, and loneliness. Social support for physical activity and for diet will be measured by 2 items adapted from the Social Support and Exercise Survey [77], with respondents asked to respond to the prompt “During the past month, how often have your friends, family or members of your household a) encouraged me to do physical activity; and, b) supported me to eat healthy foods.” Response options will be on a 5-point scale (1=none of the time to 5=very often or always).

Self-efficacy for healthy eating will be measured by the 7-item healthy eating scale of the Healthy Eating and Weight Self-Efficacy scale [78]. Response options are on a 5-point Likert scale (1=strongly disagree to 5=strongly agree). This subscale has good internal consistency (α=.81) and adequate test-retest reliability (*r*=0.72) [78]. An additional question, specific to the SSBC Australia program, was added “based on my knowledge of glycaemic index (GI), I am able to choose foods that are low GI.”

Self-efficacy for physical activity will be measured by an adapted version of the exercise self-efficacy scale, which has shown good internal consistency (α=.92) and construct and criterion validity [79]. Participants will be asked “How confident are you right now that you could achieve your physical activity goals if ...” for 4 of the scenarios (felt pain when exercising, did not enjoy it, too busy with other activities, and felt tired) and 1 scenario (were in a bad mood) adapted from the feeling stressed or feeling depressed items. Response options are on an 11-point scale from 0=not confident to 10=very confident.

Loneliness will be measured using a single-item measure, which asks “How often do you feel lonely?” 1=often or always to 5=never [80].

###### Health-Related Measures

Health-related quality of life will be measured by the EQ-5D-5L [81], with registration for the use of this project obtained on July 2, 2024. This is collected as an effectiveness outcome and for its potential use for economic evaluation. The EuroQol-5D-5L asks participants to rate their health today on a visual analogue scale, where 0 is the worst health you can imagine, and 100 is the best health you imagine. It also asks participants to rate their level of difficulty (1=no problems to 5=extreme problems) with 5 dimensions (mobility, self-care, usual activities, pain or discomfort, and anxiety or depression). Their health states reported on these items will be converted to utility scores (where 0 represents dead and 1 represents full health), using value sets [82] consistent with reported norms for the Australian population [83]. The utility scores can be used to derive quality-adjusted life years.

Diabetes and prediabetes status are not effectiveness outcomes of such a short intervention but will be assessed at each time point by a single multiresponse question, along with the date of any diagnosis that occurred.

Health care use is collected in the preprogram and 12-month surveys for its potential in estimating economic benefit. Participants are asked to report over the last 12 months their number of emergency department presentations, urgent care clinic presentations, day-only hospital admissions, overnight hospital admissions (including the number of nights spent in hospital), as well as the number of times they visited each of the following: general practitioner or family doctor, allied health professional, and specialist. The questions were designed to be broadly consistent with most health care use measures [84], adding in urgent care clinics, which are a relatively new health care service in Queensland, Australia, that are designed to reduce hospital admissions and emergency department presentations.

Adverse events will be collected for trial monitoring and to inform the APEASE criteria of side effects or safety. The coach will record any adverse events occurring during sessions. Clients will be shown anything their coach recorded and asked if they have experienced any new problems with their health since they started the program (at the end of the program) or since they were last asked (at 3, 6, and 12 months post program). They will be prompted to include any new diagnoses of medical conditions or illnesses, any periods of hospitalization or surgery, any muscle injuries, bone or joint problems, or any new symptoms or worsening of preexisting conditions and told they do not need to mention anything their coach already recorded. For up to 5 problems per time point, they will be asked to describe the problem, rate the likelihood it was related to program participation (highly unlikely or unlikely or about 50:50 chance or likely or highly likely or I do not know), and the severity of the problem (mild or moderate or severe).

#### Maintenance

Sustainability of the program will be measured yearly by the Short Program Sustainability Assessment Tool (version 2.0) [85], with the measure completed by site and organizational leads. This tool measures sustainability across 8 domains: environmental support, funding stability, partnerships, organizational capacity, program evaluation, program adaptation, communications, and strategic planning. Each domain has 3 statements (24 in total) with a 7-point response scale for each statement (1=to little or no extent to 7=to a very great extent) as well as a “not able to answer” option. The average score in each domain and the average total score will be considered.

Data on membership conversions and retention rates will be collected at quarterly intervals from the site-level client-management system and considered at both a site and organizational level.

Maintenance of client-level outcomes will be assessed in 2 ways. Primarily, effects will be considered maintained if there is still an improvement over preprogram levels that is present following a period of noncontact after completion of the intervention. Secondarily, the degree of change from the end of the program will be evaluated against a margin of error (δ) to determine whether outcomes are worsened (by an amount more than δ), further improved (by an amount more than δ), or maintained (unchanged to within ±δ). The primary end point for maintenance is 12 months, with other time points (3 and 6 months) collected to inform how long effects might be maintained.

#### Data Management

REDCap (version 15.0.7) will be used to collect all survey data for the coaches and clients, the client clinical assessment measures, and the implementation checklists. REDCap is a mature, secure web application for building and managing online surveys and databases. It provides automated export procedures for seamless data downloads to Microsoft Excel and common statistical packages and reporting features to facilitate project management. Qualtrics will be used for the organization- and site-level survey data collection. Any additional data collection (eg, interview recordings, meeting minutes, and participant tracking) will be stored on The University of Queensland Research Data Manager with access only provided to those named on the ethics. This research data manager will also be used to store any combined deidentified datasets. These deidentified datasets will be used for data pooling with the Canadian implementation of the SSBC program as required to address additional research questions beyond just the Australian evaluation. All staff and students involved in this study will be provided with sufficient training in the collection of data and entry into all applications. To comply with the Australian Code for the Responsible Conduct of Research [86], research data will be retained for a minimum period of 15 years from the date of publication. A deidentified datasets will be uploaded to a data repository following publication of the primary papers.

#### Data Analysis

Context, adoption, reach, implementation, and sustainability outcomes will be described. To evaluate client-level effectiveness and maintenance, changes from pre- to postintervention, as well as over the relevant maintenance time points, will be assessed using linear mixed models, correcting for repeated measures and cluster (site) using random intercepts, and adjusting for baseline values of the outcome. Analyses will be of evaluable cases, adjusting for predictors of missing data, with sensitivity analysis involving multiple imputation to test the robustness of conclusions to missing data handling choices. Effectiveness of the training will be assessed by describing competency attainment and testing changes from pre- to posttraining in confidence and knowledge scores, using 2-tailed paired *t* tests or nonparametric paired tests as appropriate. These tests ignore clustering due to the expected very small sample within each of the Y sites as well as the fact the training is provided centrally (unlike the intervention). Instead, exploratory analyses will test effectiveness in relevant subgroups (eg, Y coaches and student coaches from Logan Healthy Living).

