#### Delivery of Program by Site (Delivery Funded by Research)

For the first 2 years, the delivery of the SSBC Australia intervention to clients will be primarily funded by the research grant, with in-kind support given by the delivery provider in relation to free gymnasium membership for the duration of the 6-session delivery (4 to 6 weeks).

Aligned with the Canadian model, the SSBC Australia intervention involves 2 key elements: the 6 individual coaching and exercise sessions with the trained SSBC coach and the client workbook.

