#### Target Sample Size—Coaches

There is no target sample size for coaches. Each Y site is required to have at least 2 trained coaches, while the Logan Healthy Living site is expected to have a small number of trained clinicians and a larger number of trained student coaches (anticipated total n≈50, mostly from Logan Healthy Living).

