#### Target Sample Size—Participants

The target sample size is 500 participants enrolled (400 from the Y Queensland sites and 100 from the Logan Healthy Living site) for the 2-year researcher-led recruitment window, with no maximum sample size. This target sample size was determined based on the anticipated feasibility of recruitment. This sample size of 500 across 5 sites is sufficient to provide 80%-90% power with 5% 2-tailed significance to detect a 60 minute per week change in self-reported MVPA, which requires sample size of 394-528 based on assumptions of *r*=0.4, SD 330, 20% attrition, and intraclass correlation=0.001 (design effect=1+0.001(100–1)=1.099) informed by unpublished data from similar programs delivered in Logan and The Y sites.

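### The client model and the design effect cluster on site only, although coaching is one-to-one and the 400 Y clients may share as few as 8 coaches; the stated power is not assured under minimum staffing once the coach ICC exceeds about 0.01

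*Protocol article*

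**What the plan says.** The section on research-funded delivery names as a key element of the intervention "the 6 individual coaching and exercise sessions with the trained SSBC coach". Individual Coaching Sessions describes a motivational-interviewing approach with check-in, planning and goal setting for each client.

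On staffing, Target Sample Size—Coaches states that "Each Y site is required to have at least 2 trained coaches". About 50 coaches are anticipated in total, mostly at Logan Healthy Living. Target Sample Size—Participants splits the 500 clients into 400 from the four Y sites and 100 from Logan.

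For the analysis, "changes from pre- to postintervention, as well as over the relevant maintenance time points, will be assessed using linear mixed models". That sentence goes on to correct for repeated measures and for cluster, with site in brackets as the cluster, using random intercepts and adjusting for the baseline value. The sample size is justified as "sufficient to provide 80%-90% power" at 5% two-tailed significance, "to detect a 60 minute per week change in self-reported MVPA", with "design effect=1+0.001(100–1)=1.099". The cluster size of 100 is a site.

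The only place where the article explains ignoring clustering concerns the coach-training tests. There it remarks that training is central, unlike the intervention.

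**The concern.** When one coach counsels many clients individually, those clients share that coach's skill and style, and their changes may be correlated. Coaches here need no professional qualification. They may be staff, volunteers or students, and the competency threshold for motivational interviewing is 0.5 of 2.0 on each criterion. Differences between coaches in client change are therefore plausible.

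The caseloads are uneven. If each Y site runs on its minimum of 2 coaches, 400 clients share 8 coaches, or 50 each. The remaining 42 of about 50 coaches would share Logan's 100 clients, at about 2-3 each. The large overall number of coaches does not dilute the clustering where most of the clients are.

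Two things are at stake: whether 500 clients give the power claimed, and whether the primary analysis can show how far the benefit depends on a few coaches. The second matters for a trial meant to inform scale-up with lay coaches.

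**Working it through.** **Inputs from Target Sample Size—Participants:** change of 60 min/week, SD 330, pre-post correlation 0.4, 20% attrition, site ICC 0.001, site size 100, two-sided 5%.

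**Reproducing the plan's figure.** SD of change = 330 × √(2 × (1 − 0.4)) = 361.5. A paired test by noncentral t needs 287 completers for 80% power and 384 for 90%.
- 287 × 1.099 / 0.80 = 394.3
- 384 × 1.099 / 0.80 = 527.5

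These match the stated 394-528, so no coach allowance is hidden in the calculation. With 500 enrolled there are 400 completers. The effective number is 400 / 1.099 = 364, and power is 88.5%.

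**Adding coach.** Assumptions: equal caseloads within each organization, one coach per client, 80% completing (320 Y, 80 Logan), 50 coaches in all. Then

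DE = 1 + ICC_coach × (Σm²/Σm − 1) + 0.001 × (80 − 1).

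- 8 Y coaches (40 completers each) and 42 at Logan (1.9 each): Σm²/Σm = 32.4
- 20 Y coaches (16 each) and 30 at Logan (2.7 each): Σm²/Σm = 13.3

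The documents give no coach ICC, so a range is shown:

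| Assumed coach ICC | DE, 20 to 8 Y coaches | Power at 500 enrolled | N for 80%-90% power, 20 Y coaches | N for 80%-90% power, 8 Y coaches |
|---|---|---|---|---|
| 0.001 | 1.09-1.11 | 88-89% | | |
| 0.005 | 1.14-1.24 | 85-87% | | |
| 0.01 | 1.20-1.39 | 80-86% | 432-578 | 500-669 |
| 0.02 | 1.33-1.71 | 72-82% | 476-637 | 613-820 |
| 0.05 | 1.70-2.65 | 53-72% | | |

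**Threshold.** 80% power needs an effective 287, so DE may be at most 400 / 287 = 1.394. With 8 Y coaches, the limiting coach ICC is (1.394 − 1.079) / 31.4 = 0.010.

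**Intervals.** Change scores were simulated (20,000 replicates) for 80 completers at each of 5 sites, with coaches nested in sites, site ICC 0.001 and z limits. With 8 Y coaches, type I error (100% minus coverage) was:

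| Assumed coach ICC | Site intercept acting on the change | No cluster term reaching the change |
|---|---|---|
| 0.01 | 6.3% | 9.8% |
| 0.02 | 7.4% | 13.2% |
| 0.05 | 9.8% | 22.7% |

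With the site intercept on the change and a coach ICC of 0.02, the mean model SE was 23.6 against a true SD of 23.5. The SE is therefore about right on average. Much of the remaining excess comes from using z limits with only 5 sites.

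**The case against.** A reader might infer that the confidence intervals simply ignore coach clustering. The usual formula at 40 clients per coach gives design effects of 1 + 39 × 0.02 = 1.78 and 1 + 39 × 0.05 = 2.95. These imply an SE too small by a factor of 1.33-1.72 and a type I error of 14%-25%. The documents do not support that reading. The formula describes an analysis with no cluster term, and the planned model has a site intercept. Coaches are recruited within sites, so their differences pass into the variance of the site means, which that intercept carries. The larger figures apply only if the site intercept acts on outcome level and cancels from the pre-post contrast. The article does not settle this, but adjusting for the baseline value points the other way.

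Three further objections have weight:
- **The coach ICC is assumed.** The only ICC in the article is 0.001 for site, from similar programs. If those programs had about two providers per site, two clients at a site would share a provider about half the time. A coach ICC above about 0.001 × 2 = 0.002 would then be hard to reconcile with that value, and the effect would be negligible. Their staffing is not described, so this is possible but not established.
- **Two coaches per Y site is a minimum.** It is not a forecast, and more coaches shrink the effect.
- **Coach variation is not wholly unseen.** Fidelity and quality are recorded at each session, a random sample of sessions is reviewed, and scripts standardise delivery. These describe delivery, though, and do not estimate variation in client change.

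**Conclusion.** The point holds, mainly for the power statement. Site is named as the cluster in both the model and the design effect, and coach is in neither, so this is a stated choice and not a detail deferred to an analysis plan. Under minimum Y staffing, 80% power at 500 enrolled is not assured once the coach ICC exceeds about 0.01. At 0.001 nothing material changes.

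The consequence for intervals is modest if the site intercept acts on the change: type I error of about 6%-10% with z limits over coach ICCs of 0.01-0.05, partly owing to having only 5 sites. A claim that type I error reaches 14%-25% should not be made against the plan as written.

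All sizes rest on assumed coach ICCs, equal caseloads within organization, one coach per client, 20% attrition and a change-score analysis.

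**What to change.** Add a coach-within-site random effect on the change to the client model, either as the primary analysis or as a prespecified sensitivity analysis. State that the site effect also acts on the change. Assign each client to the coach who delivered most of the sessions. The article does not say that clients keep one coach, and since placements can last as little as 5 weeks and delivery up to 6, handovers may occur. Report the between-coach SD of change. Restate the power in Target Sample Size—Participants over a stated range of coach ICCs and numbers of Y coaches.

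The coaches already complete session checklists in REDCap, so the coach should be recoverable for each session without new data collection. The costs are slightly wider intervals, a coach variance that will be imprecisely estimated (a few large caseloads and many of about 2), majority-coach assignment that is only approximate where coaches change, and a less favourable power figure.

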## Methods

### Study Design

In line with the SSBC Canada evaluation, SSBC Australia will be assessed via a type 2 hybrid effectiveness-implementation cluster nonrandomized single-arm trial, where the primary effectiveness outcome will be end-of-program change in self-reported moderate- to vigorous-intensity physical activity (MVPA) behavior, and the primary implementation outcome will be fidelity of program delivery within the provider settings. The study design with respect to establishing effectiveness is a cluster single-arm pre- and posttrial. The evaluation period is 4 years; however, research funding for site-level implementation is provided for the first 2 years only. The evaluation is facilitated by the research team across the 4 years. The timeline for adaption, delivery, and evaluation is shown in Table 1.

**Table 1 table1:** Timeline of the project.

	Year 1	Year 2	Year 3	Year 4	Year 5
Site-level adaptations	✓				
Research-funded delivery		✓	✓		
Site-funded delivery				✓	✓
Research evaluation		✓	✓	✓	✓

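### Adjusting a single-arm pre-post change for its own baseline understates the standard error under ordinary readings of the model sentence; the clause should be dropped or its standard error specified

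*Protocol article*

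**What the plan says.** Study Design: "The study design with respect to establishing effectiveness is a cluster single-arm pre- and posttrial", and "the primary effectiveness outcome will be end-of-program change in self-reported moderate- to vigorous-intensity physical activity (MVPA) behavior". The quantity to be estimated and tested is therefore a mean change in one group.

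Data Analysis: changes from pre- to postintervention, and over the maintenance time points, are assessed in linear mixed models "correcting for repeated measures and cluster (site) using random intercepts, and adjusting for baseline values of the outcome". On the analysis set: "Analyses will be of evaluable cases, adjusting for predictors of missing data". The article does not say whether the preprogram value is also a response, how many waves enter one model, which reference distribution is used, or whether the standard error of the adjusted change allows for sampling error in the baseline mean.

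Target Sample Size—Participants: 500 clients are said to give "80%-90% power with 5% 2-tailed significance to detect a 60 minute per week change in self-reported MVPA". The assumptions are r=0.4 and "SD 330, 20% attrition, and intraclass correlation=0.001", with "design effect=1+0.001(100–1)=1.099", leading to a requirement of 394-528.

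Table 6 places movement behaviors, which include MVPA, at five waves: preprogram, end-of-program, and 3, 6 and 12 months. Health-related quality of life and loneliness have four waves, and the in-person measures have three.

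**The concern.** In a two-arm comparison, baseline adjustment removes noise and the baseline mean drops out of the contrast. With one arm nothing drops out. Regressing change (or follow-up) on centred baseline returns the raw mean change as the point estimate. The software's default standard error, however, contains only the residual variance around the regression line and takes the observed baseline mean as a known constant. For the population mean change that variance is too small, and the error always runs toward false positives.

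The single-arm pre-post test carries the effectiveness claim on its own. The primary maintenance criterion, improvement over preprogram levels at 12 months, is the same kind of contrast and would be affected in the same way. The sample size rests on the unadjusted change variance, so under this reading the power calculation and the test would use different variances.

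**Working it through.** **Inputs.** r=0.4, SD=330, 20% attrition, design effect 1.099, difference 60 min/week and two-sided 5%, all from Target Sample Size—Participants. Evaluable n = 500 × 0.8 = 400. Assumptions of this check: equal variances at each wave, equal correlation between all waves, normal data, and five equal sites of 80 where site is modelled.

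**1. Reproduce the plan's sample size.**
- Change SD = 330 × sqrt(2(1−0.4)) = 330 × sqrt(1.2) = 361.5.
- A one-sample t test on the change needs 287 clients for 80% power and 384 for 90%.
- 287 × 1.099 / 0.8 = 394.3, and 384 × 1.099 / 0.8 = 527.5. This matches 394-528.
- With the baseline-adjusted variance, SD²(1−r²), the normal approximation gives about 274 and 367. The plan was therefore sized on the unadjusted change.

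**2. Change or follow-up as response, centred baseline as covariate.**
- Sampling SE of the mean change: SD × sqrt(2(1−r)/n) = 361.5 / 20 = 18.1.
- Default model SE: SD × sqrt((1−r²)/n) = 330 × sqrt(0.84) / 20 = 302.4 / 20 = 15.1.
- Ratio: sqrt((1−r²)/(2(1−r))) = sqrt((1+r)/2) = sqrt(0.7) = 0.837.
- Actual type I error: 2(1−Φ(1.96 × 0.837)) = 10.1%.
- Over other correlations: 11.4% at r=0.3, 9.0% at 0.5, 8.0% at 0.6 and 7.1% at 0.7.
- Simulation under no change, site ignored: 10.2% (3,000 runs), against 4.8% for the paired test on the same data. With four follow-up waves and a participant random intercept: 10.2% (8,000 runs).

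**3. Add the site random intercept that the sentence specifies.** With REML and a z test, the adjusted model gave 8.2% (intraclass correlation 0) and 8.4% (0.001). The unadjusted change with the same site intercept gave 3.9% and 4.1%, so the covariate still about doubles the rate. With a t reference on 4 df, the adjusted model gave about 1.5%.

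**4. Preprogram value as both response and covariate, participant random intercept.** In units of SD², the within-person mean square is 1−r = 0.6.
- Two waves: the between-person mean square given baseline is (1−r²)/2 = 0.42. This is below 0.6, so the participant variance is set to zero and the two are pooled to about 0.51. SE = 330 × sqrt(2 × 0.51/400) = 16.7; ratio 16.7/18.1 = 0.922; type I error 7.1% (simulated 6.7%). Here the cause is the deflated residual variance, not a baseline mean taken as known.
- Three waves: the variance of the participant mean given baseline is (2 × 0.84 + 2 × 0.24)/9 = 0.24, so the mean square is 3 × 0.24 = 0.72. This exceeds 0.6, the participant variance stays positive and the time contrast keeps its correct SE. Simulated type I error: 5.1% with three waves and 4.5% with five.

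**5. After correction.** The unadjusted change, or the adjusted mean with b²s₀²/n added to its variance (b the slope on baseline, s₀² the baseline variance), gave 4.8% (intraclass correlation 0) and 5.6% (0.001, site ignored).

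**The case against.** The strongest reply is that the inflation needs a model the article does not fix. MVPA is measured at five waves and the sentence speaks of repeated measures with random intercepts, so a joint model with the preprogram value among the responses is a natural reading. Step 4 shows that the error rate is then nominal. The 10% figure also leaves out the stated site intercept, and a small-cluster reference would more than offset the inflation. Response vector, covariance structure and degrees of freedom are details an article may leave to a fuller plan. The adjusted standard error is also valid conditional on the observed baselines. Finally, the point estimate is unaffected, and at the design difference of 60 min/week z = 60/18.1 = 3.3, significant either way.

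Most of this stands, and it limits the point. A reader might infer that the standard error is too small for every client-level outcome and that the primary test certainly runs at 7% to 10%. The documents do not support that. Depending on the reading, the rate at r=0.4 runs from about 1.5% to about 10%. The secondary maintenance comparison, change from end of program, contrasts two follow-up waves, and a covariate constant across waves cancels there.

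What does not stand is that this is only missing detail. The baseline covariate is a stated rule. It gains nothing for a single-arm mean change under any reading, and nothing in the sentence secures the harmless version. Validity conditional on the observed baselines does not settle it either, since the trial is meant to inform expansion to other sites, which makes the population mean change the natural target.

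**Conclusion.** The point holds conditionally. With change or follow-up as the response and the default standard error, the SE is about 16% too small (15.1 against 18.1 min/week), and the nominal 5% test runs at about 10%, or about 8% with a site intercept and z test. With the preprogram value used twice over two waves, the rate is about 7%. With three or more waves and a participant random intercept the covariate does no harm and no good, and with a 4-df reference the test is conservative. These figures rest on r=0.4, about 400 evaluable clients and equal correlation between waves.

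A reader might also infer that the sample size is wrong because it uses a different variance. It is not: 394-528 is reproduced from the unadjusted change variance, which is the right one for this target. The analysis wording is what should move. Should-fix, moderate confidence.

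**What to change.** For the mean-change estimand, delete the baseline-adjustment clause from the Data Analysis section. Fit one repeated-measures model per outcome with the preprogram value as a response alongside the later waves, time as a categorical fixed effect, a participant random intercept or unstructured within-person covariance, and the site effect. Test the time contrasts against preprogram. State the reference distribution used with five sites. If baseline is kept as a covariate, say that the standard error of the adjusted change adds the sampling variance of the baseline mean (b²s₀²/n).

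The cost is one or two sentences, no new data and no change to the sample size. Intervals would be up to about 20% wider than under the change-on-baseline reading (1/0.837 = 1.195). Client recruitment began only in September 2025, so the wording can be settled before analysis.
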